## Abstract

**Background:**

Hypertension is a major risk factor for cardiovascular diseases. Acupuncture has been used to control blood pressure in clinical, however, the high-quality clinical evidence is insufficient and the underlying mechanisms remain unclear.

**Objectives:**

This study aims to evaluate the efficacy of electroacupuncture for patients with essential hypertension (EH) compared with sham electroacupuncture and explore the neural mechanism.

**Study design and methods:**

his is an 8-week, parallel-grouped, randomized clinical trial. A total of 66 patients diagnosed with EH are randomly assigned (1:1) to receive either the electroacupuncture or sham electroacupuncture treatment 3 sessions per week for 4 weeks. The primary outcome is the mean systolic blood pressure change at week 4 from the baseline measurement. The independent sample t-test will be used to compare the differences between two groups. The secondary outcomes include the change in mean diastolic blood pressure, the proportion of patients with controlled blood pressure (< 140/90 mm Hg), and quality of life. The outcome variables are measured at baseline, week 2, week 4 and week 8. Functional magnetic resonance imaging scans, pulse rate variability acquisition, and image-based photoplethysmography recording are performed at baseline and the end of the intervention period to explore acupuncture-related neuroplasticity changes. Correlation analyses are performed to investigate the relationships between the neural changes and clinical symptoms. Adverse events during the trial are monitored.

**Trial registration:**

Chinese Clinical Trials Registry, the number is: ChiCTR2400082315 (https://www.chictr.org.cn/showproj.html?proj=223840).

## Background

Hypertension is a common risk factor for cardiovascular diseases, accompanied by increased blood pressure and autonomic dysfunction, which can cause a wide range of damage to the brain, heart, and blood vessels [1,2]. It is estimated that more than 30% of adults worldwide suffer from hypertension, with a huge economic burden on society [3,4]. Long-term elevation of blood pressure could exacerbate brain degeneration in hypertensive patients, leading to an increase in the risk of cardiovascular events [5,6]. Surveys of blood pressure-related diseases show that about 13.5% of global premature deaths (about 7.6 million people) are attributable to hypertension [7]. However, the awareness and control of hypertension remain insufficient in many countries [8], and 87% population of the nearly 300 million patients with hypertension in China have poorly controlled blood pressure [9].

Antihypertensive drugs are often used to hypertension treatment, but existing some adverse effects and low adherence [10]. The guidelines recommend lifestyle modifications also as first-line therapy for hypertension patients, but are difficult to maintain in the long-term [11]. Therefore, it is important to seek effective adjuvant treatment of hypertension. Acupuncture has been used as a non-pharmacological treatment for cardiovascular diseases [12,13], and some studies suggest that acupuncture could lower blood pressure [14–16]. However, a Cochrane review showed that the efficacy of acupuncture on the reduction of blood pressure is still not widely recognized due to insufficient high-quality clinical evidence [17].

It is suggested that the imbalance in the autonomic nervous system with enhanced sympathetic activity is one of the pathogenesis of hypertension, which is controlled by key brain nuclei and neural circuits in the central nervous system [18,19]. Studies have found that the regulation of autonomic parameters is associated with lower blood pressure in hypertensive people [20]. However, whether acupuncture regulates blood pressure by affecting the autonomic nervous system and the central mechanism is unclear. Functional magnetic resonance imaging (fMRI) could observe the functional activity changes of the brain, and in recent years, it has been used to explore the central mechanism of acupuncture effect [21]. In addition, contact and image-based photoplethysmography (PPG) could detect important body physiological and pathological information (e.g., pulse rate variability [PRV] and blood pressure) from the transformed pulse wave signal to detect autonomic neuromodulation, and they also could be used as the non-invasive quantitative indicators of sympathetic and parasympathetic tone and functional status in clinical practice [22–24]. Based on the above, we aims to perform a randomized controlled clinical trial in patients with essential hypertension (EH) to evaluate the efficacy and safety of electroacupuncture (EA) vs. sham electroacupuncture (SE). The second objective is to preliminarily assess the underlying central integration mechanism of acupuncture on reducing blood pressure by combining neuroimaging and neural detection techniques.

## Methods and design

### Study design

This is a randomized controlled, parallel trial. A total of 66 participants will be recruited for the study, with an average of 33 in each group. The protocol will be reported following Standard Protocol Items: Recommendations for Interventional Trials (SPIRIT) schedule statement (S1 File) and the Standards for Reporting Interventions in Clinical Trials of Acupuncture (STRICTA) guidelines (S2 File). The schedule of enrolment, intervention, and assessments is shown in Fig 1. The procedure of the trial is shown in Fig 2.

**Fig 1 pone.0332268.g001:**
[figure not shown]
Schedule of enrollment, intervention, and assessment. Schedule of enrollment, intervention, and assessment. SBP, systolic blood pressure; DBP, diastolic blood pressure; SF-12, 12-item Short Form Health Survey; IPAQ, International Physical Activity Questionnaire; PSQI, Pittsburgh Sleep Quality Index; STAI-S, State-Trait Anxiety Scale-State Anxiety Subscale; fMRI, functional magnetic resonance imaging; PRV, pulse rate variability; PPG, photoplethysmography.

**Fig 2 pone.0332268.g002:**
[figure not shown]
Flow diagram. EH, essential hypertension.

### Study setting and recruitment

The study will be carried out at the Dongzhimen Hospital Affiliated to the Beijing University of Chinese Medicine. The study will recruit participants with EH who meet the diagnostic criteria according to the European guideline [25] and Chinese guideline [26] through hospital outpatient. Meanwhile, the recruitment of participants starts in September 2024. This study recruitment period is expected between September 2024 and October 2025. The trial is planned to be completed in December 2025. Additionally, 33 healthy controls (HCs) will be recruited through social media advertisements.

### Participants

#### Inclusion criteria.

Meeting the diagnostic criteria for EH, according to the European and Chinese guidelines for hypertension.Office systolic blood pressure (SBP) from 140 to 159 mm Hg and diastolic blood pressure (DBP) from 90 to 99 mm Hg.Not taking any antihypertensive medication.Aged 25–60 years, male or female, right-handedness.No language or intellectual disabilities for answering and completing the questionnaires.Willing to sign the informed consent.

#### Exclusion criteria.

Other diseases that can affect the blood pressure, including but not limited to diseases of renal parenchyma, renal artery stenosis, obstructive sleep apnoea syndrome, and primary hyperaldosteronism.Receiving medicines that affect blood pressure except antihypertensive drugs in last month, including but not limited to glucocorticoids and central nervous system inhibitors.Uncontrolled diabetes (HbA1c≥6.5%).Drug or alcohol abuse.Pregnant and lactating women.Having fMRI contraindications, such as pacemakers, defibrillators, vascular clips, implanted electrical or magnetic devices, mechanical heart valves, cochlear implants, and claustrophobia; engaged in metal related work with metal fragments in the face or eyes; severe skull anatomical asymmetry or definite lesions were found in MRI scanning.Received acupuncture treatment for hypertension within 3 months.Participated in other clinical trials in the past 1 months.

### Informed consent and participant safety

Patients will be asked to sign an informed consent form prior to enrollment (provided in the S3 File). During the trial, the researchers will monitor and record adverse events and reactions throughout the acupuncture treatment, such as panic, subcutaneous hematoma, and pain. If the patient is unable to tolerate these adverse effects, they will be allowed to withdraw from the study.

### Randomization

In this study, EH patients will be randomly divided into an EA group and a SE group in a ratio of 1:1, with 33 participants in each group. The random sequence will be generated by a independent statistician (not involved in the implementation or statistical analysis) with the software Stata V.12.0 using block randomization, with a block size varying randomly between 4 and 6. Allocation concealment is implemented by a dedicated random number administrator. The random numbers will be kept by a same personnel who is not involved in the treatment and clinical measurement of this study. After the baseline assessment of eligible patients, a random number and group will be told to the acupuncturist by this fixed person via a mobile phone message.

### Sample size

The sample size is calculated based on the decrease in SBP from baseline to week 4. According to the prior research [27–30], we assume that the mean SBP change value at week 4 in the EA group reaches 5 mm Hg with a standard deviation of 5 mm Hg, and in the SE group, the mean SBP change value reaches 1 mm Hg with a standard deviation of 5 mm Hg. The sample size of 26 patients in each group was calculated to provide 80% power, with a two-tailed α level of 0.05, using PASS 2021 software. This requires 33 patients per group allowing for 20% dropout.

### Interventions

#### Electroacupuncture.

Patients will receive 12 sessions of electroacupuncture treatment (3 sessions weekly for 4 weeks). The acupoints will include bilateral *Hegu* (LI4), *Quchi* (LI11), *Zusanli* (ST36), and *Taichong* (LR3) (Table 1 and Fig 3), according to WHO Standard Acupuncture Locations. These acupoints are selected based on previous research and existing evidence, their combined use has a synergistic effect in lowering blood pressure [27,31]. Another multicenter clinical trial of acupuncture for hypertension also supported the clinical efficacy of the combined use of these acupoints [32]. Furthermore, the mechanism reseach suggested that electroacupuncture stimulation of Taichong and Quchi could effectively reduce the blood pressure and the excitability of sympathetic nerve in the hypothalamic paraventricular nucleus (PVN) in spontaneous hypertensive rats [33]. Electroacupuncture stimulation of Zusanli might affect blood pressure by regulating the function ofγ-aminobutyric acid receptors in the nucleus solitularis [34]. Acupuncture intervention at the Taichong could reduce the blood pressure of spontaneously hypertensive rats and inhibit the activity of nicotinamide adenine dinucleotide phosphate oxidase in the lateral ventral medulla oblongata of their heads [35].

**Table 1 pone.0332268.t001:** Locations of acupoints for electroacupuncture group.

Acupoints	Locations
Taichong (LR3)	In the depression anterior to the junction of first and second metatarsal bones.
Zusanli (ST36)	3 cun* directly below Dubi (ST35), and one finger-breadth lateral to the anterior border of the tibia.
Hegu (LI4)	On the dorsum of the hand, radial to the midpoint of the second metacarpal bone.
Quchi (LI11)	On the lateral aspect of the elbow, at the midpoint of the line connecting LU5 with the lateral epicondyle of the humerus.

*1 cun (≈20 mm) is defined as the width of the interphalangeal joint of patient’s thumb.

**Fig 3 pone.0332268.g003:**
[figure not shown]
Locations of bilaterally acupoints and non-acupoints. LI, large intestine meridian; LR, liver meridian; ST, stomach meridian;NA, non-acupoint.

Before needle insertion, both the acupuncturist’s hands and acupuncture site will be strictly disinfected with 75% alcohol. Then, single-use acupuncture needles (0.30 * 40 mm, Hwato, Suzhou, China) will be inserted vertically into acupoints, and acupuncturists will manually stimulate the needles (twirling, lifting, and thrusting) to achieve ‘de qi’ sensation (soreness, numbness, distension or heaviness). For each treatment, paired electrodes from the Hwato SDZ-II EA apparatus (Suzhou, Jiangsu Province, China) will be attached to needle holders at LI 4–LI 11 and ST 36–LR 3 acupoints on one side of the body. Attach the EA apparatus to the opposite needle holders at the next treatment. The EA stimulation will be a dilatation wave of 2 Hz, depending on the patient’s comfort level (Fig 4). The treatment will be left for 30 min.

**Fig 4 pone.0332268.g004:**
[figure not shown]
The operational diagram of the intervention. EA, electroacupuncture; SE, sham electroacupuncture.

#### Sham electroacupuncture.

Four non-acupoints are preset for sham electroacupuncture treatment. The location of the non-acupoints is shown in Table 2 and Fig 3. Acupuncture is a treatment method that stimulates specific acupoints along the meridians on the body surface. These non-acupoints locations are areas near or around the actual acupoints and without therapeutic effect. The acupuncture needles and disinfection procedures will be the same as the electroacupuncture group. The acupuncture needles will be inserted into the skin 4 mm without manipulations or ‘de qi’ sensation. Paired electrodes from the Hwato SDZ-II EA apparatus (Suzhou, Jiangsu Province, China) will be attached to needle holders at NA 1–NA 2 and NA 3–NA 4 points on one side of the body without electric current output. At the next treatment, the sham EA apparatus will be attached to the opposite needle holders (Fig 4). This shallow puncture method could avoid the introduction of confounding factors (such as skin contact effects) due to different stimulation methods, and increase the success rate of blinding for patients (penetrating operations are closer to the real treatment experience). The duration of the treatment will be left for 30 min. The patient will receive 12 sessions of EA treatment (3 times a week for 4 weeks).

**Table 2 pone.0332268.t002:** Locations of non-acupoints for sham electroacupuncture group.

NA	Locations
NA1	1 cun beside LR3, on the first metatarsal bone.
NA2	1 cun back and outside of ST36.
NA3	In the middle of LI4 and LU10 (between the lung and large intestinal meridian).
NA4	In the middle of LI11 and LU5 (between the lung and large intestinal meridian).

NA non-acupoints.

*1 cun (≈20 mm) is defined as the width of the interphalangeal joint of patient’s thumb.

All the above treatments were carried out by licensed acupuncturists with at least three years of acupuncture experience. The acupuncturist will keep a record of each treatment. During the trial, patients will maintain the same lifestyle as before. If the patient’s blood pressure is poorly controlled, we will consult with a professional doctor to help the patient develop an effective antihypertensive therapy. Medication regimens will be recorded. The HCs with normal blood pressure will not receive any intervention.

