### Clinical outcome assessments

The primary outcome will be the mean difference in the changes in office SBP from baseline to 4 weeks between the two groups. SBP will be measured using a unified automated monitor (HEM-7136, Omron, Kyoto, Japan), and follow the WHO STEPS protocol for the procedure. The arm with higher blood pressure in the patient at baseline will be selected as the measurement arm throughout the study. Before each measurement of the patient’s blood pressure, the patient will be asked to sit and rest for 5 minutes with the upper arm at the level of the heart. Then, the blood pressure measurement will record three values in succession at 5-minute intervals, and the final blood pressure being the average of the last two times [36,37].

Secondary outcomes will include differences in the changes in office DBP between the two groups; the proportion of patients with well-controlled blood pressure (office blood pressure <140/90 mm Hg); and differences in the changes in the quality of life assessed using 12-item Short Form Health Survey (SF-12) [38]; physical activity assessed using International Physical Activity Questionnaire (IPAQ) [39]; quality of sleep assessed using Pittsburgh Sleep Quality Index (PSQI) [40]; the severity of current anxiety symptoms assessed using State-Trait Anxiety Scale State Anxiety Subscale (STAI-S) [41].

Safety outcomes will be any acupuncture-related adverse events (pain, panic, and subcutaneous hematoma) at weeks 2, 4, and 8 in both groups. All patients will be asked to guess which treatment they have received at week 2 and week 4 as blinding assessments. All patients’ physical condition, cognitive function, or other eligibility will be monitored during the trial.

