### Statistical analysis

#### Clinical data analysis.

The clinical data will be analyzed by an independent statistician using IBM SPSS V.20.0 software, and the *P* values < 0.05 will be considered statistically significant. For those conforming to a normal distribution, the data will be described utilizing the mean (standard deviation), otherwise, the median (quartile spacing) will be used. The categorical data will be described as percentages (%). We will use the independent sample t test to compare the effect of EA vs. SE on blood pressure from baseline to week 4. For the other outcomes, if data conforms to a normal distribution, it will undergo t-test analysis. Conversely, if it does not conform to the normal distribution, it will be analyzed by nonparametric test. Categorical data will be analyzed via the χ^2^ test or Fisher’s exact test. All cases of randomized patients will be undertaken on the intention-to-treat analysis, and missing values will be filled in using multiple imputations. To evaluate the stability of results, we will conduct a sensitivity analysis with the last observation values. A per-protocol analysis will include the patients who complete at least 80% of the study.

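### Antihypertensive drugs may be started during the trial, but the control endpoint and every stated analysis use post-drug readings unchanged, so a drug-controlled patient counts as a success of the assigned arm

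*Protocol article*

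**What the plan says.** Under Inclusion criteria, patients must be free of antihypertensive drugs at entry, with "Office systolic blood pressure (SBP) from 140 to 159 mm Hg and diastolic blood pressure (DBP) from 90 to 99 mm Hg". The last paragraph under Sham electroacupuncture, which covers both arms, allows drugs to be added later: if a patient's "blood pressure is poorly controlled, we will consult with a professional doctor to help the patient develop an effective antihypertensive therapy". It says that regimens are recorded and gives no further use for that record.

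Under Clinical outcome assessments, the primary outcome is the between-group difference in change in office SBP to week 4. One secondary outcome is "the proportion of patients with well-controlled blood pressure (office blood pressure <140/90 mm Hg"; it carries no condition on drug use. According to the Abstract, outcomes are measured at baseline and at weeks 2, 4 and 8.

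Under Clinical data analysis, the blood pressure comparison is an independent-sample t test. All randomised patients are analysed by intention to treat, missing values are multiply imputed, and a sensitivity analysis uses last observations. The remaining set is defined by completion: "A per-protocol analysis will include the patients who complete at least 80% of the study".

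**The concern.** The stated aim is the efficacy of electroacupuncture against sham. Once a drug is added, a patient's pressure reflects both the drug and the randomised treatment.

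For the control endpoint this misclassifies: a patient who needed a drug because the assigned treatment did not suffice, and who then falls below 140/90, is scored as a success of that treatment. For SBP and DBP, the comparison moves by the difference in drug use between arms times the drug effect. Week 8 is the most exposed, because there has been more time for drugs to be started and the 4-week treatment course is over.

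The regimens are recorded, so drug starts could be tabulated, but none of the stated analyses would separate the two effects.

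**Working it through.** **1. Following one patient through the stated rules.** Take a patient who starts a drug before week 4 and attends the visit.

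- Intention to treat: the reading is observed, so it is not imputed and enters the t test as it stands.
- Last-observation analysis: the week-4 value exists, so nothing changes.
- Per-protocol set: membership depends on completion, so the patient and the reading stay in.
- Control endpoint: any reading below 140/90 is a success.

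No stated rule treats this patient differently from one who took no drug.

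**2. The plan's own figure.** The Sample size section rests on three inputs. For electroacupuncture: "the mean SBP change value at week 4 in the EA group reaches 5 mm Hg with a standard deviation of 5 mm Hg". For sham: "the mean SBP change value reaches 1 mm Hg with a standard deviation of 5 mm Hg". Testing is planned "with a two-tailed α level of 0.05". The difference is 5 − 1 = 4 mm Hg with SD 5. At 26 per arm the noncentrality is 4 / (5 × √(2/26)) = 2.88. The two-sample t test then has 80.7% power (79.1% at 25), which agrees with "The sample size of 26 patients in each group was calculated to provide 80% power". With 20% dropout, 26 / 0.8 = 32.5, rounded up to 33. The sample size is not in dispute.

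**3. Illustration for SBP.** The documents give neither a drug-start rate nor a drug effect, so both are assumed: starts by week 4 of 15% in sham (SE) and 5% in electroacupuncture (EA), and a drug effect D of 10 mm Hg (range 5 to 15).

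Mean fall = planned fall + p × D:
- SE: 1 + 0.15 × 10 = 2.5
- EA: 5 + 0.05 × 10 = 5.5
- Difference: 3.0 mm Hg

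Power depends on who starts.

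(a) Starts at random within arm: variance = 25 + p(1 − p)D².
- SE: 25 + 0.1275 × 100 = 37.75
- EA: 25 + 0.0475 × 100 = 29.75
- Average 33.75, SD 5.81

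(b) Starts in those with the smallest falls: a covariance term −2 × D × 5 × φ(z_p) is added, where φ(z_p) is 0.233 for 15% and 0.103 for 5%.
- SE: 37.75 − 23.3 = 14.4
- EA: 29.75 − 10.3 = 19.4
- Average about 16.9, SD about 4.1

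Power at 26 per arm (noncentral t for random starts, simulation for smallest falls):

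| Drug effect (mm Hg) | Difference (mm Hg) | Power, random starts | Power, smallest falls |
|---|---|---|---|
| none | 4.0 | 81% | 81% |
| 5 | 3.5 | 66% | about 82% |
| 10 | 3.0 | 45% | about 74% |
| 15 | 2.5 | 26% | about 52% |

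**4. Other patterns, D = 10, random starts.**
- Equal use, 10% in each arm: the difference stays 4.0, SD = √(25 + 0.09 × 100) = 5.83, power 68%.
- Reversed use, EA 15% and SE 5%: difference = (5 + 1.5) − (1 + 0.5) = 5.0, an inflation.
- No true effect, 20% against 5%: a spurious difference of 0.15 × 10 = 1.5 mm Hg, significant about 14% of the time instead of 5%.

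**5. Illustration for control.** Consider SBP only and assume baseline SBP uniform on 140 to 159. About 13% of sham patients fall below 140 without drugs. With 15% starting at random and D = 10, this rises by about 7 points (about 3 to 10 points for D from 5 to 15). If drugs go only to the 15% with the highest SBP, the rise is about zero.

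**The case against.** The strongest reply is that intention to treat normally means using the observed value whatever treatment was added. That is a legitimate treatment-policy analysis, and details on added medication often sit in an analysis plan that is not shown here. This stands in part: the intention-to-treat comparison should remain. It does not dispose of the point, because the control definition, the per-protocol rule and the permission to start drugs are all fixed in this article, and together they score a drug-produced reading as success.

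The objections to size also stand. Every start rate and drug effect is assumed, and starts within four weeks may be few. The 45% figure needs drugs to be given without regard to response.

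A reader might infer more than the documents support:

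- *That every patient qualifies for drugs at entry, so the criteria contradict each other.* All patients do enter above the control threshold. But *poorly controlled* is left undefined; nothing makes it the complement of *well-controlled*, and the clause describes a consultation during the trial.
- *That unblinded staff would start drugs by arm.* Acupuncturists know the allocation, but they take no part in outcome assessment. The clause brings in a doctor, and nothing says that the doctor knows the arm. Differential use is possible, not shown.
- *That the bias always dilutes the effect.* It does so if sham patients start more often and reverses if EA patients do.
- *That 15% of sham patients would become responders.* That is a ceiling, reached only if the drug takes every starter across the threshold.

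**Conclusion.** The point holds for the rules as stated. The control endpoint misclassifies any patient whose pressure is brought below 140/90 by a drug started in the trial, whatever the start rate. The SBP and DBP comparisons estimate a mixture of drug and acupuncture effects, and the article neither names this as the intended estimand nor plans an analysis that separates them.

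The size is illustrative only. With 15% of sham and 5% of EA patients starting a drug worth 10 mm Hg, the difference goes from 4.0 to 3.0 mm Hg, and power at 26 per arm from 81% to between about 45% and 74%. At 5 mm Hg, with starts in those with the smallest falls, there is no power loss. The direction is not fixed by anything in the article. The documents do not support a claim that the primary result is necessarily biased to a material degree, nor that the entry and drug-start wording are in outright contradiction.

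**What to change.** Settle the following before unblinding:

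1. **Control endpoint.** Count a patient who started an antihypertensive drug before the assessment as not controlled. The rate regardless of drugs may be shown beside it.
2. **SBP and DBP.** Keep the intention-to-treat analysis as primary and name it as treatment-policy. Add one prespecified supplementary analysis that sets readings after a drug start to missing and handles them with the multiple imputation already planned.
3. **Per-protocol analysis and reporting.** State that post-drug readings are excluded from the per-protocol analysis, and tabulate drug starts by arm and date.
4. **Wording.** Reconcile the concomitant-care paragraph with Clinical outcome assessments, so that it is clear how *poorly controlled* relates to the stated control threshold. No clinical rule is proposed here.

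The cost is some wording, one extra analysis and slightly lower control rates. The medication data are already being recorded, and the sample size need not change.
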